### Disaster research and Project Ice Storm

Our approach to PNMS research is to study pregnant women experiencing natural disasters. By their nature, disasters tend to have sudden onsets and are generally considered to be “independent stressors”. Using disasters as natural experiments in PNMS research presents an approximation of the randomization afforded by laboratory animal studies, and capitalizes on the relatively large potential subject pool following a disaster to a large community.

The first prospective study of prenatal stress from a natural disaster was Project Ice Storm [46] in Canada. Project Ice Storm (http://www.mcgill.ca/projetverglas/) was initiated soon after a series of ice storms struck Southern Québec in January 1998 resulting in power outage for more than 3 million people for as long as 6 weeks during the coldest months of the year, and causing 27 deaths. The Insurance Bureau of Canada and Environment Canada count the ice storm as the worst and most costly natural disaster in Canadian history. Project Ice Storm was designed to clarify the role of PNMS in a prospective longitudinal design. Women who had been pregnant during the ice storm, or who became pregnant within three months of the storm, completed questionnaires about their objective exposure to hardship because of the storm (e.g., levels of threat, loss, change, and scope), and about their degree of distress (post-traumatic stress-like symptoms) due to the storm; they also provided saliva samples to assess diurnal cortisol patterns. Project Ice Storm mothers and children are still being followed more than 15 years later.

Effects of PNMS from the ice storm have been found in nearly every domain of child development examined. Significant effects of the degree of maternal objective exposure to the disaster (but not maternal subjective distress) have been found on the children’s cognitive development [47-49], obesity [50], insulin secretion [51], brain development [52], and epigenetic signatures [53]. Effects of maternal subjective distress (and to a lesser extent, objective exposure) have been found on fingerprint asymmetry [54], autistic-like traits [55], and diagnoses of asthma [56] throughout childhood. Objective exposure and subjective distress from the ice storm have been found to interact such that the worst child outcomes are associated with mothers who presented a mismatch between objective exposure and subjective distress, that is, children of mothers with high objective stress but low subjective distress, or with low objective stress along with high distress [55]. There have also been significant timing effects: early pregnancy exposure seems to represent a window of vulnerability for cognition at age 2 years [47], and autism-like traits at age 6½ years [57], while second trimester exposure was associated with shorter gestation lengths and other birth outcomes [58], while worse motor outcomes have been associated with exposure in late pregnancy [59]. The sex of the child has often been found to moderate effects of PNMS: girls were found to be more vulnerable to effects of PNMS on asthma-related symptoms and diagnoses [56] and motor functioning [59], while boys seem to be more vulnerable for effects on fetal growth [58].

Although the Project Ice Storm sample is relatively small (n < 200), statistical power is enhanced by having a range of exposure levels from mild to severe; by the fact that the degree of exposure to the disaster was independent of family psychosocial attributes; by the acute onset of the event which allows exact dating of the stressor in the pregnancy; and by having detailed information on the women, their exposures, and their distress gathered relatively soon after the disaster. The independent nature of the disaster reduces the need to identify and control for all potential confounders, and allows one to disentangle the effects of the women’s objective exposure to the event from their cognitive appraisal of it, and from their subjective distress and hormonal responses.

Project Ice Storm has many limitations, however. It suffers from the fact that women were first recruited 5-6 months after the crisis such that, for half of the women, the reports of storm events were given only after birth. It is difficult to combine diurnal cortisol data collected from women who were still pregnant, and from others who had already given birth, at the time of sampling. Although Project Ice Storm has advanced the PNMS field, it requires replication with (1) another type of disaster, (2) speedier recruitment and baseline data collection, (3) data collected from the pregnant women before the disaster struck to be able to control for pre-disaster psychopathology, (4) assessments starting earlier in childhood and better long-term retention, (5) biological samples from mother, placenta, and fetus to test hypotheses about physiological mechanisms in PNMS and interactions, and (6) with an intervention to buffer the potential effects of PNMS.

### The 2011 Queensland floods, the M@NGO trial, and QF2011

The Australian state of Queensland experienced severe flooding, the worst in 30 years, in early-January 2011 affecting more than 200,000 people in more than 70 towns. Three quarters of Queensland was declared a disaster zone with more than $1 billion of reported damages: flooding reached its peak in the state capital of Brisbane on January 10th. Residents of 2,100 Brisbane streets were told to evacuate and 20,000 homes were inundated. Approximately 35-40 deaths have been attributed to the floods. Two studies have published results on the effects of these floods on the perceived physical and mental health of residents. Researchers using random-digit dialing telephone surveys of more than 6,000 residents between March and June of that year found that 62 % of respondents reported being affected by Queensland’s severe summer weather events “in any way”, including property damage (as much as 37 % for those in some suburbs), with 2 % living elsewhere at least temporarily [60]. Income was reduced for 17 % of respondents. Trauma impacts ranged from feeling “terrified, helpless or hopeless” (14 %) to thinking they might be “badly injured or die” (4 %). Up to five months after the summer disaster, 7 % of respondents reported being “still distressed” and 9 % were “worried about how they would manage”. Results from a self-report postal survey (n = 960) conducted in July 2011 indicated that having been directly impacted by the floods (i.e., residence or vehicles affected by flood waters) was associated with increased risk of worse overall (OR = 5.3) and worse respiratory (OR = 2.3) health, greater psychological distress (OR = 1.9), and problems sleeping (OR = 2.3), and with symptoms reflecting probable post-traumatic stress disorder (PTSD) (OR = 2.3) [61, 62]. As response rates from both studies were less than 50 %, results are not generalizable to the entire population. Nonetheless, these results suggest that the Queensland floods of 2011 had significant impacts on health, including distress in the general population; nothing is known from these studies about effects on pregnant women, however.

The QF2011 Queensland Flood Study was designed to address the shortcomings of Project Ice Storm and other PNMS research. QF2011 subjects were recruited either through a pre-existing clinical trial or, after the floods, directly into the study outside of the clinical trial.

The January 2011 floods occurred during the active recruitment period for a large, unrelated study of pregnant women. Since June 2010, the Mater Mothers' Hospital (MMH) in Brisbane had been involved in a multi-site randomized controlled trial (RCT) called the M@NGO trial (Midwives @ New Group practice Options (Trial registration: Australian New Zealand Clinical Trials Registry ACTRN12609000349246)) [63, 64]. This study pitted standard antenatal care against caseload midwifery care provided within a Midwifery Group Practice (MGP). Approximately 300 Brisbane women had already been recruited into M@NGO prior to the floods, and recruitment continued until the pre-determined end of M@NGO recruitment across all sites on May 31, 2011. For the full M@NGO trial, power analyses had determined that a sample size of 750 women was required to detect a difference, with 80 % power and a type 1 error of 5 %, in the primary, obstetric end-points for the M@NGO Trial; the secondary outcomes of the trial were determined through questionnaires offered at 6-12 weeks and 6 months postpartum [63]. Women were eligible for inclusion in M@NGO regardless of risk factors, and were recruited for the trial at less than 24 weeks of pregnancy, at which time psychosocial and demographic data were gathered.

Participants were randomly assigned to receive one of two forms of care: standard care (public hospital-based care or shared care with general practitioners) in which prenatal, labor, birth and postnatal care is provided by on duty staff – both midwives and doctors; or MGP which provides each woman with a primary midwife who coordinates and provides continuity through prenatal, labor, birth and postnatal domiciliary care (up to six weeks postpartum). The primary midwife is supported by her MGP colleagues (typically 3-4 midwives/MGP) who provide back up in the absence of the primary midwife. In this study, births occurred in-hospital with the primary midwife coordinating higher level care as needed, for women with identified risk factors. A key feature of this model is continuity in care provision with women having 24/7 access to their primary or back-up midwife [65, 66]. A 2013 Cochrane review of 13 trials (16,242 women) found midwife-led continuity of care was associated with benefits for mothers and babies, with no identified adverse effects compared with models of medical-led care including shared care [65, 66]. Benefits found included reductions in fetal loss prior to 24 weeks’ gestation, preterm birth, epidural anesthesia, episiotomies, and instrumentally assisted birth. Women’s chances of being cared for in labor by a known midwife, and having a spontaneous vaginal birth, were also increased in the midwifery-led continuity care model, as were the rates of maternal satisfaction [65, 66]. Expanding on the previous MGP literature described above, the M@NGO trial was the first to test continuity of care without excluding women at higher obstetric risk at trial entry; as such, the M@NGO participants represent a more real-world sample than in previous MGP research.

The ‘active ingredients’ of the MGP intervention are not completely understood [67, 68]. The 24/7 access to a known midwife, resuts in more personalized access to care if needed. Having a known midwife providing care in labor and the early postpartum period, and having postpartum support for several weeks if required may provide a buffer from psychosocial stress [66]. The power of MGP perinatal care to protect pregnant women and their fetuses against psychological stress (whether due to disasters, bereavement, or other hardships) is currently unknown; the subgroup from the M@NGO trial included in the QF2011 study may provide valuable data on the benefits of this model of care as an intervention to buffer against stress.

Following the Queensland flood, the QF2011 study was ‘piggy-backed’ onto the M@NGO trial. QF2011 recruited additional pregnant women to create a larger sample size, with M@NGO participants as an important embedded subgroup. The QF2011 recruitment questionnaires included assessments of maternal exposure to, and stress arising from, the floods. The QF2011 protocol included biological sampling from the birth and from the newborn, and added measures of maternal and infant outcomes at 6-12 weeks and 6 months postpartum to the M@NGO protocol, as well as re-administration of the flood-related assessments 12 months post-flood (January 2012). QF2011 also includes direct assessments of the mothers and their children at ages 16 months, 2½, and 4 years.

### Problem statement, objectives, hypotheses and research questions

Retrospective human studies suggest that maternal exposure to a natural disaster or other severe stressors increases the fetus’ risk for disorders in childhood and adulthood. Animal studies, human studies of life events or anxiety, and retrospective epidemiological studies all have a number of limitations that compromise the internal validity of the study design or its conclusions, and tell us little about the active ingredients of the prenatal stress effect.

The overall aim of this project is to replicate, expand, and improve upon findings from Project Ice Storm to increase understanding of the mechanisms responsible for the effects of maternal exposure to varying levels of hardship imposed by a severe, independent stressor: a natural disaster. We will determine the effects of various aspects of maternal stress due to the 2011 Queensland floods on the mother, her pregnancy and her infant, and the extent to which these effects may be moderated by other biological, psychological, and social factors. We will also determine whether MGP care can be shown to buffer pregnant women and their unborn children against any effects of the floods.

The primary research question that QF2011 will address is the following: **To what extent will the mothers’ objective exposure, cognitive appraisal, subjective distress, and cortisol levels from the 2011 Queensland floods explain variance in outcomes for the mother, the pregnancy, and the unborn child?** More specific hypotheses and research questions are presented below.By what biological mechanisms do different components of the stress experience (e.g., objective, subjective) get translated through the Maternal-Placental-Fetal (MPF) axis to influence development of the unborn child?

Although much research on fetal-programming by PNMS is conducted on rodents, the functioning of the human placenta is distinct from that of rodents, and no appropriate animal model exists. To date, no human studies have been able to show the links between an objective environmental stressor, placental function and neurodevelopmental outcomes. It is also unknown how the cascade of stress through the MPF axis, emerging from objective stress, differs from those of subjective distress. To understand how PNMS affects the MPF axis, three hypothetical models will be studied:

**Model 1:***MPF neuroendocrine systems*. We propose that objective and subjective PNMS will activate a cascade of events leading to an increase in maternal, placental, and fetal cortisol terminating in altered HPA axis function and a lower stress response in the child. We predict that more severe objective/subjective PNMS will decrease activity of the placental/activity of the placental 11β-HSD2, resulting in increased levels of cortisol in placenta and fetal blood (cord blood). Moreover, more severe objective/subjective PNMS will also be associated with increased placental Corticotropin-releasing hormone (CRH) production that will, in turn, over-stimulate the maternal HPA axis and thus exacerbate maternal cortisol production and the inhibition of placental 11β-HSD2, resulting in higher levels of cortisol in placenta and fetal blood (cord blood).

**Model 2:***MPF immune systems and metabolic outcome*. We propose that more severe objective/subjective PNMS will be associated with increased maternal catecholamine levels (physiological response to stress) resulting in an abnormally high level of oxidative stress and pro-inflammatory cytokines in the placenta that will increase inflammatory and oxidative status of maternal and fetal blood, which will cause an increase risk in obstetric complications (such as preterm birth, low birth weight, intrauterine growth restriction and preeclampsia), which may then go on to predict future risk for metabolic and psychiatric difficulties in children later in life.

**Model 3:***Birth weight and body composition*: We propose that higher placental cortisol levels will cause a decrease in the production of placental hormones regulated by glucocorticoids (such as human placental lactogen (hPL), placental growth hormone (pGH), leptin, estrogens, progesterone, and glucose transporter type 1(GLUT1; lower maternal-fetal glucose exchange)) resulting in a lower placental efficiency (lower birth weight and higher placental weight), resulting in fetal growth restriction and/or altered programming of body composition in the child. We hypothesize also that maternal and fetal glucose, insulin, leptin, and other adipocytokines in blood will be involved in this process.

We also hypothesize that the effects observed in models 1-3 in placental function and in children will be more important for male fetuses compared to female fetuses.(2)Midwifery Group Practice (MGP) care (in comparison with standard care) will protect pregnant women and their unborn children from the impact of objective levels of exposure and subjective levels of maternal distress arising from the 2011 Queensland floods.

Project Ice Storm found multiple effects of objective stress exposure on child outcomes*.* Although psychosocial treatments may reduce maternal anxiety and subjective stress after a disaster [69], they cannot alter the objective hardship and danger that was faced. Because QF2011 is piggy-backed onto the M@NGO study, we have a built-in RCT of prenatal care that commenced before the flooding that may demonstrate protective properties of this more personalized, and supportive, coordinated midwifery approach. We hypothesize that MGP care will buffer effects of flood stress (objective and/or subjective) on maternal outcomes, such as PTSD symptoms and depression, on perinatal outcomes (e.g., gestation length and birth weight), and on child outcomes.(3)Maternal and child genotypes will moderate the effects of PNMS on outcomes. Some examples of such gene-by-environment interactions are listed here:Maternal mental health:i.We hypothesize that maternal PTSD symptom severity (1 year post flood) may be explained by interactions between objective stress (especially Threat) and the maternal 5-HTTLPR (serotonin-transporter-linked polymorphic region) of the *SLC6A4* gene, controlling for potential confounders.ii.Postpartum (and continuing) maternal depression may involve interactions between objective stress (especially Loss) and the maternal 5HT2A gene (serotonin receptor 2A), controlling for potential confounders.Child stress reactivity:i.The effects of PNMS on the child’s HPA axis will be moderated by infant genotypes associated with the stress response, such as CRH, CRHR1.Epigenetics: Since Project Ice Storm has shown that maternal objective stress predicts DNA methylation in children at age 13 years [70], QF2011 will also endeavor to obtain biological samples throughout childhood for testing epigenetic hypotheses at a later date.(4)Does maternal sensitivity mediate, or moderate, (or both) the effects of PNMS on child outcomes?

Research suggests that the post-natal environment may buffer the effects of prenatal maternal mood on child outcomes. [name]’s group found that maternal sensitivity moderated the impact of maternal antenatal anxiety on the child’s cognitive and behavioral outcomes at 7 months [45, 71]. There are no data, however, on whether maternal sensitivity can moderate the effects of an independent prenatal maternal stressor on child outcomes. By the same token, it is unknown whether an objective, independent stressor in humans will influence maternal behaviors, like sensitivity, which may then mediate effects of PNMS on the child. Thus, we hypothesize that objective exposure and subjective stress from the floods will predict HPA stress reactivity and cognitive development in QF2011 infants, and that this association may be mediated and/or moderated by maternal sensitivity.(5)How do pre-existing levels of depression interact with peritraumatic responses to the Queensland floods to influence the trajectory of maternal mental health following exposure?

Because a measure of perinatal depression (the Edinburgh Postnatal Depression Scale (EPDS)) is administered routinely to all women in Australia at the time of hospital booking, levels of pre-existing maternal depression are available for our subgroup of QF2011 women who had already booked at the Mater hospital prior to the floods. Therefore, the QF2011 study is in a position to respond to unanswered questions about the natural history of maternal mental health in response to a disaster. We predict that depression before exposure to the disaster will interact with levels of distress and dissociation at the time of the flooding (i.e., ‘peritraumatic’) to explain variance in postpartum levels of depression, anxiety, PTSD-like symptoms, and positive mental health.(6)If variance in physical characteristics, like fingerprint asymmetry and finger length ratios, are explained by levels of objective and subjective PNMS, what biological processes are they markers for?

[name] and [name] have found that PNMS from the Québec ice storm explains significant variance in physical markers associated with neurodevelopmental disorders, such as dermatoglyphic (fingerprint) asymmetry [54], and the ratio of the lengths of the second and fourth fingers (2D:4D ratio) which is reputed to reflect *in utero* exposure to testosterone [72, 73]. But it is unknown by what process PNMS influences 2D:4D ratios and dermatoglyphic asymmetries. Once it is determined which biological variables in placenta and cord blood are sensitive to PNMS, we will determine which of these, if any, are then correlated with these neurodevelopmental markers in hands.(7)To what extent do the severity of prenatal maternal objective/subjective stress, and/or maternal cortisol during pregnancy pre-flood, predict the HPA axis function of the infant/child, and what other outcomes are associated with altered HPA axis function?

Prenatal maternal stress research, particularly in animal models, has demonstrated the effects of PNMS on the development of the fetal HPA axis, which regulates the stress response (Glover et al., [74]; Charil et al., [5]). In humans, fetal exposure during early to mid-pregnancy, the period during which the HPA axis develops, seems particularly deleterious [75, 76]. Alterations in HPA axis have also been shown to be associated with a wide range of neurodevelopmental, psychiatric and metabolic outcomes [74, 77]. We aim to determine whether it is mere objective exposure to the stressor, or the maternal subjective distress, that accounts for altered HPA axis function in the infant/child, and which outcomes (e.g., attention, emotional difficulties, learning and memory recall, obesity) are associated with altered function.

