## Methods/design: QF2011

### Participants

All women who agreed to participate in the study provided written informed consent. Inclusion and exclusion criteria differed slightly for M@NGO [63, 64] and for QF2011. Women were eligible for recruitment to the M@NGO trial if they were less than 24 weeks pregnant and were not planning caesarean section birth; QF2011 participants had to have been pregnant with a singleton pregnancy (at any gestation) and residing in the general vicinity of Brisbane on January 10, 2011. All participants were 18 years of age or older at recruitment, and were able to speak English fluently.

Recruitment for QF2011 began as soon as ethics approval was received (April 4, 2011), and continued to mid-January 2012 (12 months after the peak of the flood); as per original protocol, recruitment for M@NGO ceased on May 31, 2011 in both Sydney and Brisbane. Recruitment proceeded in 4 ways:When new participants were recruited into M@NGO, they were also presented with the QF2011 protocol, and invited to participate in either or both studies. M@NGO recruitment at the Mater Hospital involved face-to-face, phone, and e-mail recruiting following a routine mail-out describing the study to all women attending the antenatal clinic.The team contacted all existing M@NGO subjects who were eligible for QF2011 first by e-mail, then by cell phone (text message), then by telephone inviting them to also participate in the new flood study.The team invited women who were pregnant and eligible for the QF2011 study, but not eligible for M@NGO, or who would have been eligible for M@NGO but were approached after M@NGO recruitment ceased, to participate in QF2011. A flyer inviting women to participate and to contact the recruitment team was included in the routine mail-out from the antenatal clinic. A researcher in the antenatal clinic actively recruited participants face-to-face on site and was available to speak to midwives and other potential participants about the study.Finally, advertisements were placed in local newspapers, on radio, and on the internet for women who were pregnant at the time of the floods (even if they had already delivered).

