As such, this study included 2 main groups of participants:QF2011 women enrolled in M@NGO (n = 108, including 1 intrauterine death). These participants were enrolled in both M@NGO and QF2011. Some were already M@NGO study participants at the time of the floods and where subsequently recruited to QF2011; others were pregnant at the time of the floods and were recruited into both studies simultaneously. At recruitment to the QF2011 study, M@NGO women may still have been pregnant or they may have already given birth as the inclusion criteria stated only that they must have been pregnant on January 10, 2011.QF2011 women not enrolled in M@NGO (n = 122). This group included women who had declined participation, did not meet the selection criteria for the M@NGO study, or who were recruited after the close of M@NGO (May 31, 2011).

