#### Data analysis and power

Our analyses of the QF2011 data will proceed in a highly structured manner, according to our underlying explanatory model. This model posits that objective stress and cognitive appraisal predict peritraumatic stress responses, which predict both subjective stress reaction (PTSD symptoms) and maternal HPA axis response. We hypothesize that at least some of these aspects of maternal stress may influence maternal mental health and may also influence variables within the placenta and fetus (cord blood); thereby influencing fetal/child physical/physiological development (growth & body composition, fingerprints or finger length ratios, HPA axis) and child neurodevelopment (cognitive, behavioral, and motor development). We further suggest that at each level of the cascade there may be genetic moderation and epigenetic mediation; and also moderation of outcomes by pre-disaster maternal characteristics (e.g., depression, socioeconomic status), and by the sex of the infant. Finally, our results may indicate a moderating effect from prenatal care (MGP versus standard care) and maternal caretaking behaviors. Below, we present a sampling of statistical approaches we will take to the data analysis.

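### The MGP buffering test is presented as an RCT in place before the flood, but not every woman in the QF2011 subgroup of 108 was randomised before it, and the subgroup was partly formed after allocation

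*Protocol article*

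**What the plan says.** Hypothesis 2, in the section on problem statement, objectives and hypotheses, is that MGP protects mothers and their unborn children from the impact of both objective flood exposure and subjective distress. Its design argument is "we have a built-in RCT of prenatal care that commenced before the flooding that may demonstrate protective properties". The outcomes it names are PTSD symptoms, depression, perinatal outcomes such as gestation length and birth weight, and child outcomes.

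The recruitment history is in two other sections:

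- The section on the floods and M@NGO gives the trial's start: "Since June 2010, the Mater Mothers' Hospital (MMH) in Brisbane had been involved in a multi-site randomized controlled trial". It then says "Approximately 300 Brisbane women had already been recruited into M@NGO prior to the floods, and recruitment continued", with the end date given as "recruitment continued until the pre-determined end of M@NGO recruitment across all sites on May 31, 2011". Entry to M@NGO required less than 24 weeks of pregnancy.
- Participants requires a singleton pregnancy and "residing in the general vicinity of Brisbane on January 10, 2011". It dates the opening of QF2011 recruitment to 4 April 2011. For women already in M@NGO, "The team contacted all existing M@NGO subjects who were eligible for QF2011 first by e-mail". New M@NGO recruits were offered either study or both.
- Participants also describes the M@NGO subgroup of 108. Some were in M@NGO when the flood came, while "others were pregnant at the time of the floods and were recruited into both studies simultaneously".

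Data analysis and power says that "our results may indicate a moderating effect from prenatal care (MGP versus standard care" and maternal caretaking, without separating women randomised before the flood from those randomised after it. The Discussion again presents the midwifery trial as an RCT embedded in the study.

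**The concern.** The argument for hypothesis 2 depends on care already being in place at the flood. The article contrasts this with psychosocial treatment given after a disaster. For a woman randomised after 10 January, MGP could not have been acting when the flood occurred, so she informs a different question: whether MGP begun later helps a woman already exposed.

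Two further features weaken the protection that randomisation is assumed to give:

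- Women already in M@NGO decided about QF2011 when already allocated to a recognisable model of care. If willingness to join depended on arm, the arms within QF2011 would no longer be comparable.
- Hypothesis 2 has MGP buffering the effect of subjective distress while also naming PTSD symptoms as something MGP may reduce. The IES-R therefore serves as both moderator partner and outcome. If MGP changes it, women with equal IES-R scores in the two arms are not exchangeable.

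At stake is how far the MGP result can be read as a randomised comparison of care in place before a disaster.

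**Working it through.** The article gives no sample size or power for the MGP contrast, so there is no figure to reproduce. The 750 belongs to the parent trial's obstetric end-points. The check is date arithmetic and a comparison of sections.

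**1. When simultaneous recruits entered.** They needed both studies open, so they entered between 4 April and 31 May 2011.
- 10 January to 4 April = 84 days; 84/7 = 12.0 weeks.
- 10 January to 31 May = 141 days; 141/7 = 20.1 weeks.

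None of these women had trial-allocated care at the flood.

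**2. A second group randomised after the flood.** M@NGO kept recruiting after 10 January and QF2011 opened on 4 April. Any woman who entered M@NGO in that 84-day gap and later joined QF2011 counts as an existing M@NGO participant, yet was randomised after the flood. Neither this number nor the number of simultaneous recruits is given.

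**3. Gestation at the flood.** With entry below 24 weeks, simultaneous recruits were below 24 − 12.0 = 12.0 weeks at the flood if entered on 4 April, and below 24 − 20.1 = 3.9 weeks if entered on 31 May. Entry date is therefore tied to exposure timing. This does not bias the comparison of arms, because women randomised on any given date share that timing whichever arm they are in. It does mean that a before/after difference in the MGP effect could not be put down to timing of care alone.

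**4. Selection into QF2011.** 108/300 = 36%, but this is not uptake among eligible women. The numerator includes women randomised after the flood. The denominator includes women who had already delivered: a woman at 13 weeks on 1 June 2010 (an assumed start day, with entry at the 12–14 weeks of Table 1) would have been at 13 + 223/7 = 44.9 weeks on 10 January. The eligible number is not given, nor is the split of the 108 by arm.

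**5. IES-R.** It covers the preceding 7 days and was taken at QF2011 recruitment, from April 2011. For women already randomised, that is a measurement under allocated care. QFOSS records flood events and losses, which care is less likely to alter.

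**6. Dilution.** If a share s of the subgroup was randomised after the flood and MGP had no effect in them on a given outcome, the average effect would be (1 − s) times the effect in the rest. Neither s nor the zero effect is in the document. The assumption is most plausible for recruitment IES-R in simultaneous recruits, measured around M@NGO entry. It is weak for later outcomes, since MGP runs through labour and birth to as late as six weeks postpartum.

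**The case against.** The claim about the RCT is literally true: the trial began in June 2010. Participants discloses that the subgroup is mixed, and the wording about MGP is tentative throughout. This stands as a defence against a charge of misstatement. It does not remove the problem, because the argument needs care in place for the women analysed and nothing ties the disclosure to hypothesis 2.

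Most outcomes named in hypothesis 2 come after months of possible MGP care, even for women randomised in April or May. This stands, and confines any dilution chiefly to recruitment IES-R. PDI and PDEQ are not named as MGP outcomes.

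Timing strata and weighting usually belong in an analysis plan, which is not shown. This is fair, and their absence is not the point. The point is a stated premise that the recruitment account does not support for the whole subgroup, together with the double role of subjective distress.

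A reader might infer more than the article supports:

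- That the MGP effect is attenuated by a known amount. The share randomised after the flood is not reported, so any percentage would be an assumption.
- That 36% shows poor and biased uptake. It is not the uptake rate among eligible women. Bias needs uptake to differ by arm, which is not shown, and the article describes one contact procedure without distinction by arm.
- That every woman chose QF2011 knowing her arm. For simultaneous recruits the order of consent and allocation is not stated.
- That the 122 women outside M@NGO would be added to standard care. The article ties the MGP question to the M@NGO subgroup.

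**Conclusion.** The point holds in limited form. The premise of randomised care already in place at the flood fails for part of the 108: certainly for the simultaneous recruits, who entered 12.0 to 20.1 weeks after it, and for any who joined M@NGO between 10 January and 4 April. The subgroup is partly selected after randomisation, which makes differential uptake by arm a possibility rather than a finding. An MGP-by-IES-R interaction, as hypothesis 2 implies, would condition on a variable that MGP may affect in women already allocated.

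The dates and recruitment routes come directly from the article. The size of any dilution or selection bias cannot be derived from it, and dilution need not apply to postpartum or child outcomes. This warrants a change in wording and analysis; it does not invalidate the comparison.

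**What to change.** - Qualify the claim in hypothesis 2, and the matching description in the Discussion, to say that part of the subgroup was randomised after the flood. Report the 108 by arm and by randomisation before or after 10 January 2011.
- Analyse the 108 by allocated arm with a before/after term. For early distress (recruitment IES-R), report the effect in women randomised before the flood. Read any before/after difference with gestational timing in mind.
- Make MGP-by-QFOSS the main buffering test, and treat IES-R as an outcome or mediator of MGP.
- Report QF2011 enrolment by arm and compare joiners with eligible non-joiners, using baseline data M@NGO already holds. Use enrolment weighting as a sensitivity analysis only.

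No new data collection is needed. The cost is a smaller sample for early distress and slightly wider intervals.
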